## Abstract

**Introduction:**

Uncertainty regarding the timing of weight bearing following ankle open reduction internal fixation (ORIF) in patients with different ankle fracture patterns remains. Traditional rehabilitation methods, including six weeks of non-weight bearing (NWB), is still a common approach in many hospitals, while some previous evidence has shown immediate weight bearing (IWB) to be beneficial.

**Method:**

32 adult participants with unimalleolar, bimalleolar or trimalleolar ankle fractures and stable fixation following ankle ORIF will be randomly allocated to either Immediate Weight Bearing (IWB) or Delayed Weight Bearing (DWB) groups. Stability of fixation is a subjective assessment made by the operating surgeon at the completion of fixation and is independent of fracture pattern. Participants in the IWB group will be allowed to weight bear as tolerated within 24 h, while participants in the DWB group will remain non-weight bearing for six weeks. Participants’ data including Olerud and Molander Ankle Score, Self-Reported Foot and Ankle Score, SF-36 health survey, time to return to work will be collected. X-rays will be assessed by orthopaedic team members for fixation-related complications including reduction loss, malreduction/malunion, implant failure and non-union. Participants data will be collected at six weeks, three and six-months post-surgery. We will determine the feasibility of a full RCT through assessing the recruitment rate, adherence rate, and drop-out rate.

**Results:**

Not applicable.

This pilot RCT will endeavour to optimise standard rehabilitation protocols post ankle ORIF.

## Introduction

1

Ankle fractures are one of the most common lower extremity injuries, with an incidence for those requiring hospital admission ranging from 71 to 180 per 100,000 person-years [[1], [2], [3]]. Scott, Jones [4] reported 203,261 cases of ankle fractures admission over 10 years in England with 75% of patients managed surgically with open reduction internal fixation. Despite the high rate of operative intervention, no consensus exists in literature or in clinical practice regarding the optimal post-operative rehabilitation protocol. Post-operative rehabilitation protocols are heterogenous in terms of timing of weight bearing and initiation of ankle motion (immediate, early: 2–3 weeks, and late: 4–12 weeks post-surgery) [5].

Traditional rehabilitation involves ankle non-weight bearing for six to eight weeks before weight bearing as tolerated. This approach aims to allow sufficient time for fracture healing to reduce the risk of fixation failure [6]. Alternative, post-rehabilitation protocols involve early weight bearing with or without early ankle motion within two weeks post-operation, aiming to create mechanical stimulus for bone healing and to improve functional recovery in patients with ankle fractures [6,7]. Despite evidence showing better functional outcomes and shorter recovery time favouring early weight bearing [8,9], concerns still exist regarding potential loss of fracture fixation. This discourages some surgeons from initiating early weight bearing for fear of fracture displacement [10]. Therefore, the traditional non-weight bearing rehabilitation protocols continue to be the most common approach over the past 10 years [5].

Systematic reviews demonstrate studies initiating weight bearing from 24 h to three weeks post-surgery can have better functional outcomes and shorter time to return to work, with no differences in the rate of complications compared with delayed weight bearing [[11], [12], [13], [14]]. However, concerns still exist around the timing of weight bearing in relation to the injury pattern, fixation stability and patients’ medical status [12,15]. Simple transverse or oblique fractures can potentially support weight bearing, where compression improves the chances of bony union compared with spiral or multi-fragmentary fractures [16,17]. Ongoing research in this field may provide further insights into the optimal post-operative rehabilitation protocols appropriate for various ankle fracture patterns.

To the best of our knowledge, despite a range of research aiming to shed light on this issue, no large-scale high-quality study has adequately compared immediate weight bearing following ankle fixation to six weeks non-weight bearing. Smeeing, Houwert [9] conducted an RCT with 115 patients randomised to either group 1 (unprotected immediate weight bearing and immediate ankle motion (within 24 h)); group 2 (protected early weight bearing in a cast (within 10 days) and ankle immobilization); or group 3 (unprotected non-weight bearing and immobilization (for six weeks). The primary outcome of the study showed a higher functional score and shorter time to return to work in patients in the unprotected immediate weight bearing group compared with the protected early weight bearing and unprotected non-weight bearing groups. This study was limited by a relatively small sample size and allowed weight bearing while also allowing range of motion exercises, making the effects of the weight bearing portion of their protocol difficult to isolate.

**Aim:** To conduct a pilot trial recruiting 32 participants with ankle fractures requiring ORIF, to assess the effects of immediate versus delayed weight bearing in the short term. This pilot RCT will test the feasibility of a full RCT through estimating the recruitment rate, adherence rate and drop-out rates for six months following their operation. The follow-on study will be a large-scale and multi-centre RCT to test whether immediate weight bearing following ankle fixation results in improved patient reported outcomes and earlier return to work without an increase in complications compared with patients managed with six weeks of non-weight bearing. The pilot trial will allow us to build the capacity and skills within our institution to effectively lead a multi-centre RCT.

## Methods

2

### Study design

2.1

We will conduct a parallel group, superiority designed, and open label pilot RCT, and randomise participants with ankle fracture and open reduction internal fixation to either immediate weight bearing (IWB) or delayed weight bearing (DWB) group post-surgery.

This study will be reported following Standard Protocol Items: Recommendation for interventional trial statement (SPIRIT) [18]. The study will be performed according to the Declaration of Helsinki. This trial has been registered with the Australian New Zealand Clinical Trials Registry (ANZCTR): ACTRN12623001107617. Ethical approval was obtained from Health and Disability Ethics Committees (HDECs). Informed consent will be obtained from all patients, informing them of the study aims, procedures and possible risks.

### Study setting

2.2

Participants will be recruited between February to December 2024 from Christchurch Hospital, a tertiary trauma centre in Christchurch, New Zealand. We anticipate the full RCT running at this centre, in addition to other secondary and tertiary hospitals in New Zealand.

### Eligibility criteria

2.3

Patients who are treated with open reduction internal fixation due to a unilateral ankle fractures will be sought for study enrolment. Stable fixation must be achieved by the operating surgeon. While subjective, this is likely to include criteria such as the patient having good quality bone, a good lag screw, and no significant unexpected comminution. Inclusion criteria will be skeletally mature patients (closed distal tibial physes) who are operated on due to closed ankle fractures. There is no upper age limit for inclusion. Fracture patterns will include isolated medial, lateral or posterior malleolus fractures, bimalleolar and trimalleolar fractures. Additionally, ankle fractures treated with an external fixator prior to definitive surgery will be included. These criteria were selected as no study has yet shown the association between the type of fractures and post-surgical outcomes (e.g., Quality of Life, Function scores, complications) [[19], [20], [21]], thus, if the other inclusion criteria are met, patients with different types of fracture will be included. Patients must be physically active (with or without walking aids) in the community before the injury and must speak English or have an interpreter available.

Exclusion criteria will include fractures where stability is still questionable following fixation, as deemed by the operating surgeon. Patients with active infection at the surgical site, any compound fracture, pathological fractures, Pilon fractures, or concurrent injuries that preclude adhering to the follow up protocol will be excluded. We will exclude participants who are unable to follow the protocol due to neurologic disorders (i.e., cognitive impairment, substance abuse, mental illness, intellectual disability, and dense peripheral neuropathy) or significant additional physical impairment (i.e. polytrauma patients with other limb, head or visceral injuries). Any fracture where syndesmosis stabilisation is required will be excluded as post-rehabilitation practices are more conservative with this type of fracture [22]. We will exclude patients whose follow up care will be provided outside of Christchurch Hospital.

### Interventions

2.4

Patients will receive pre-operative ankle x-rays as their primary imaging modality. CT scans will be obtained if deemed necessary by the orthopaedic team for surgical planning. All patients will be treated by orthopaedic registrars, fellows or consultants according to their preferred techniques. After surgery, all included patients will be placed in a moonboot (also known as a walker boot, or CAM boot). The moonboot consists of a rigid outer shell providing structural support for the foot and ankle, and inner padding to reduce pressure points. They can be removed for monitoring of the wounds. It allows for weight bearing while restricting ankle movement. Patients will be instructed to keep their moonboots on at all times, and to keep their wounds dry. Patients in the IWB group will bear weight as tolerated within 24 h. They will be encouraged to stand or walk without using walking aids. It is envisaged that patients in the IWB group will self-limit the amount of weight they put through their ankle based on their pain tolerance and physical fitness. If necessary, walking aids (crutches, walking frames etc.) will be provided as determined by the treating doctors, nurses, physiotherapists and occupational therapists. Patients in the DWB group will use walking aids (crutches, walking frames etc.) for mobilising and remain non-weight bearing for six weeks prior to allowing weight bearings as tolerated.

At approximately two weeks post-surgery, all patients will have their wounds reviewed in the outpatient clinic. Patients will then have their wounds redressed and be placed back into their moonboot to further 4 weeks.

### Data collection

2.5

Patient baseline characteristics and hospital data will be collected through electronic medical records during hospitalisation and at discharge by research team members. The data will consist of participants demographics including age, sex, weight, height, BMI, ethnicity, pre-injury level of activity, smoking status, medical comorbidities, and employment status, injury characteristics including date of injury, mechanism of injury, and fracture classification, and treatment details including the date of surgery, type of fixation, and hospital length of stays. We will also record these data from patients who were excluded due to the surgeon deeming fixation unsuitable for immediate weight bearing. This will allow us to further identify if any particular demographic is disproportionately excluded, and minimise the risk of bias in our sample selection for both this pilot, and the full RCT. This will enhance the inclusion and patient selection process in the full RCT.

### Outcomes

2.6

#### Primary outcome measures

2.6.1

We will assess recruitment rate, adherence rate, and drop-out rate. We will use an eligibility criteria log to screen participants eligibility. The recruitment rate will be calculated as the proportion of enrolled participants to screened participants and the number of enrolled participants per month. Adherence rate will be identified by the proportion of participants who followed the weight bearing status to all participants at their allocated arm. This will be assessed through participants interviews at the end of the study. Drop-out rate will be measured through the proportion of participants who withdraw from the study after randomisation to those who initially enrolled in the study.

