### Recruitment procedure

2.7

The research administrator ([name]) at the centre will make the first approach for screening and explaining the study to potential participants. Eligible participants who are interested in our study will be provided with the information sheet and encouraged to consult with their GPs, family and friends about the study. They will be given adequate time to consider participating in the study prior to their operation. Informed consent for study participation will be obtained prior to surgery. Retrospective data collected from Christchurch Hospital theatre records showed 291 ankle fractures (excluding those with syndesmosis fixation) were operated on during a 12-month period. On the assumption that 50% of these patients would meet the inclusion criteria and agree to participate in our study, we estimate completing recruitment within one year.

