## Statistical analysis

3

Descriptive statistics will be used to report participants’ recruitment rate per month, proportion of participants enrolled from the total number screened, adherence rate and the drop-out rate. Specific criteria to determine the feasibility of this study will be a recruitment of two participants per month, the adherence rate of 85 %, and the drop-out rate of ≤20 %.

SPSS (version 28.0; IBM Corporation, Armonk, NY) will be used for statistical analysis. We will report mean and SD for continuous data (OMAS, SEFAS, SF-36, time to full weight bearing, time to return to work and pre-injury activities) and percentage or number for categorical data (total and individual complications).

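### Adherence to a six-week restriction is measured only by an end-of-study interview, and the unstated scoring of participants who leave can make the 85% and 20% feasibility criteria incompatible

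*Protocol article*

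**What the plan says.** Section 2.6.1 makes recruitment, adherence and drop-out the primary outcomes. On adherence it says: "Adherence rate will be identified by the proportion of participants who followed the weight bearing status to all participants at their allocated arm". On source and timing: "This will be assessed through participants interviews at the end of the study". Drop-out is the "proportion of participants who withdraw from the study after randomisation to those who initially enrolled in the study".

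Section 3 (Statistical analysis) turns these into feasibility criteria: two participants recruited per month, "the adherence rate of 85" per cent, and drop-out of no more than 20%.

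Other sections fix the timing. Section 2.4 ends the DWB restriction at six weeks. Section 2.6.3 and Table 1 schedule clinic visits at two weeks, six weeks, three months and six months, with research visits from six weeks onward. Section 2.7 says: "Informed consent for study participation will be obtained prior to surgery". Table 1 and section 2.8 place eligibility and allocation after surgery, once the surgeon has confirmed stable fixation.

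**The concern.** There are two linked weaknesses in the adherence measure and a smaller one in drop-out.

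**Timing.** The behaviour of interest in DWB is over by week six, but the only stated measurement comes at the end of follow-up. Early weight bearing in DWB is the contamination that would dilute the contrast in the full trial, so a pilot should measure it well. Recall over several months is a weak basis, and a participant who has left cannot give that interview.

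**Scoring.** The denominator is everyone allocated, while the data source covers only those still present at the end. No rule links the two. Depending on the rule chosen later, the same data can pass or fail the 85% criterion, and a failure could reflect late withdrawal rather than poor adherence.

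**Drop-out base.** The numerator counts withdrawals after randomisation. The denominator is those initially enrolled, a term the article does not define. The numerator also names withdrawal without saying whether loss to follow-up counts.

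**Working it through.** **Inputs.** Pilot size 32, from 13 per group plus 20% drop-out (section 2.10). Allocation 1:1 in blocks of 4, so 16 per arm (section 2.8). Criteria of 85% and at most 20% (section 3). Restriction of six weeks (section 2.4). Last visit at six months (Table 1).

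**The plan's own figure.** 2 × 13 = 26, and 26 × 1.2 = 31.2; rounding up to a whole number gives 32. Dividing by 1 − 0.2 instead gives 26 / 0.8 = 32.5, so 33. The stated 32 is close enough for this point.

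**Recall interval.** Six months is about 26 weeks. 26 − 6 = 20 weeks, or about 4.5 months.

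**Counts that meet each criterion, out of 32.**
- Drop-out: 0.20 × 32 = 6.4, so at most 6 withdrawals.
- Adherence: 0.85 × 32 = 27.2, so at least 28 adherent.

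**Best possible adherence if w participants leave, stay in the denominator and cannot be scored adherent: (32 − w) / 32.**

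| w | Drop-out w/32 | Best adherence | Drop-out criterion | 85% reachable? |
|---|---|---|---|---|
| 4 | 12.5% | 28/32 = 87.5% | met | yes |
| 5 | 15.6% | 27/32 = 84.4% | met | no |
| 6 | 18.8% | 26/32 = 81.3% | met | no |
| 7 | 21.9% | 25/32 = 78.1% | not met | no |

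**Per arm of 16.** 0.85 × 16 = 13.6, so 14 must be adherent. 0.20 × 16 = 3.2, so 3 withdrawals pass drop-out, but the best adherence is then 13/16 = 81.3%. Under the same scoring rule the conflict appears at 3 withdrawals in one arm.

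**Alternative rule: only interviewed participants in the denominator.** With 6 withdrawals, 0.85 × 26 = 22.1, so 23 of 26 (88.5%) are needed. That is attainable, so the conflict depends on the scoring rule.

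**Chance of meeting both criteria.** These are exact binomial calculations, pooled over 32, with independent withdrawals. The true rates are assumed; they are not in the documents.

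| Drop-out | Adherence among those remaining | All allocated, leavers not adherent | Interviewed only |
|---|---|---|---|
| 10% | 95% | 0.496 | 0.949 |
| 15% | 95% | 0.235 | 0.791 |
| 15% | 100% | 0.464 | 0.805 |

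**Drop-out base, only if enrolled means consented.** The share excluded at surgery is assumed, over a range of 0 to 30%. The number consented is 32 / (1 − share), rounded.

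| Excluded at surgery | Consented | Most withdrawals that pass | Rate over randomised |
|---|---|---|---|
| 0–5% | 32–34 | 6 | 6/32 = 18.8% |
| 10% | 36 | 7 (7/36 = 19.4%) | 7/32 = 21.9% |
| 20% | 40 | 8 (8/40 = 20.0%) | 8/32 = 25.0% |
| 30% | 46 | 9 (9/46 = 19.6%) | 9/32 = 28.1% |

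The two effects act in opposite directions. The adherence base can produce an undeserved fail, and a consent-based drop-out base can produce an undeserved pass.

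**The case against.** **The conflict is conditional.** This objection stands. It disappears if leavers are interviewed on exit, scored up to withdrawal, or left out of the denominator. A scoring rule may also sit in a fuller document that is not shown. What the article itself fixes is the end-of-study interview and the all-allocated denominator, and those two do not fit together without a rule. A reader might infer that the criteria contradict each other outright; the text does not support that.

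**Good adherence in immediate weight bearing (IWB) could hide poor adherence in DWB.** A reader might infer this because section 2.4 says "It is envisaged that patients in the IWB group will self-limit the amount of weight they put through their ankle" and section 3 gives one 85% figure. Pooled, 16/16 plus 12/16 is 28/32 = 87.5%, a pass with DWB at 75%. But section 2.6.1 refers to participants in their allocated arm, which reads naturally as a rate per arm, and DWB would then visibly fail. Nor does almost any behaviour count as adherent in IWB: section 2.4 expects weight bearing within 24 hours, so a patient who stays off the ankle has not followed the allocation.

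**Drop-out is counted over those enrolled before surgery.** A reader might infer this from the timing of consent. The article does not say so. The abstract describes the 32 as those to be randomly allocated, and section 2.5 calls patients ruled out by the surgeon excluded. Enrolled may simply mean randomised, in which case nothing is diluted.

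**The criteria do not stop the trial mechanically.** Section 4 leaves continuation to discussion among the investigators. This stands and limits the consequence, although section 3 still names these figures as the feasibility criteria.

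**Some weight-bearing data will exist earlier.** Section 2.6.2 takes time to full weight bearing without walking aids from patient logs at periodic visits. The article does not name these logs as the adherence source, and that variable would not capture partial early loading in DWB.

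**Conclusion.** The point holds in a limited form. The firm part needs only one reading, that the end of the study is the six-month visit: adherence to a six-week restriction is measured once, about 4.5 months after that restriction ends, with no interview from anyone who has left.

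The collision between the criteria rests on a further assumption, that leavers remain in the denominator and cannot be scored adherent. Under it, 5 or 6 withdrawals out of 32 meet the drop-out criterion while putting 85% out of reach, and the pooled criteria are compatible only up to 4 withdrawals (12.5%). Dilution of drop-out is a question of definition: it arises only if enrolled means consented, and it changes the pass limit in these calculations from about 10% surgical exclusion upward.

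This is worth correcting before recruitment because week-six adherence cannot be recovered later. It does not show that the pilot's feasibility decision must come out wrong.

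**What to change.** 1. Record adherence at the existing 2-week and 6-week visits with two short questions, for example the date of first weight bearing and, in DWB, any weight bearing before six weeks. An end-of-study interview can remain as a supplement.
2. Use all randomised participants as the adherence denominator, score those who leave on their status up to last contact, and state how anyone without any contact after discharge is counted.
3. Report adherence against 85% in each arm, as section 2.6.1 already suggests, and say so in section 3.
4. Define drop-out over randomised participants, and count loss to follow-up together with withdrawal. Define enrolled wherever the term is used.

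The cost is two questions at visits already scheduled and a few reworded definitions. No visits or staff are added.

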### Sample size

2.10

The minimum clinically important difference for the OMAS was reported 10.5 at three months [24]. Considering the average standard deviation at 16 from prior studies, this gives a sample size of 50 per group for the main trial to achieve 90 % power at a two-sided alpha of 0.05. Given a 20 % drop-out, we will need 120 participants in total for the full trial. In order to minimise the sample size of the pilot and main trial combined, and considering the medium effect size of 0.66, it is recommended that 13 participants per group are recruited for the pilot study [31]. Given a drop-out rate of 20 %, we will need a total of 32 participants for the pilot trial. It is anticipated that these patients will carry over to participate in the ongoing full RCT, pending a successful pilot RCT, ethics approval and appropriate funding.

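### The 20% drop-out criterion counts only participants who withdraw, so it does not test the 20% loss on which both sample sizes depend

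*Protocol article*

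**What the plan says.** Section 2.6.1 of the Protocol article makes drop-out one of three primary outcomes and gives its formula: "Drop-out rate will be measured through the proportion of participants who withdraw from the study after randomisation", with the number enrolled at the start as the denominator.

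Section 3 turns the three rates into feasibility criteria: "a recruitment of two participants per month, the adherence rate of 85 %, and the drop-out rate of ≤20"%. It does not widen the definition of drop-out and adds no criterion for completeness of follow-up.

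Section 2.10 uses the same word and figure for planning. For the main trial: "Given a 20 % drop-out, we will need 120 participants in total for the full trial". For the pilot: "Given a drop-out rate of 20 %, we will need a total of 32 participants for the pilot trial", starting from 13 per group.

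Patient-reported outcomes are collected at six weeks, three months and six months (section 2.6.3). The main-trial calculation is based on the three-month OMAS difference.

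**The concern.** One word carries two meanings. In section 2.6.1 drop-out is an act by the participant, namely withdrawing. In section 2.10 it is an allowance added to an evaluable sample size. Such an allowance does its job only if it covers every randomised participant without a usable outcome, whether that person withdrew, was lost to follow-up or missed the visit or questionnaire. Section 2.10 does not spell this out, but its totals do not deliver the stated power otherwise.

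Someone who misses the three-month research visit without withdrawing is therefore counted as retained by the criterion and as lost by the analysis. The pilot could report its drop-out criterion as met, and appear to confirm the 20% planning figure, while the share without OMAS is higher. The full trial would then be planned on an allowance that is too small. Section 2.10 also expects pilot patients to carry over into the full trial, so their missing outcomes would be inherited.

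**Working it through.** **Inputs from the documents.** Difference 10.5 points, SD 16, two-sided alpha 0.05, power 90%, 50 per group, 120 in total, 13 per group and 32 in total for the pilot, drop-out 20% (section 2.10); limit of at most 20% (section 3); 1:1 allocation (section 2.8).

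**Assumed inputs.** The rates of withdrawal and of silent loss (no outcome, no withdrawal). The documents give neither, so a range is shown.

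**1. The plan's own figures.** Effect size = 10.5/16 = 0.656. For a two-sample t test the noncentrality is 0.656 × √(n/2). At n = 50 per group this is 0.656 × 5 = 3.28, and power is 0.901, so the stated 50 is reproduced. The totals follow from multiplying by 1.2: 100 × 1.2 = 120, and 26 × 1.2 = 31.2, rounded up to 32.

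**2. What the limit allows.** 6/32 = 18.75% and 7/32 = 21.9%, so the criterion is met with at most 6 counted drop-outs among 32.

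**3. Probability of meeting the drop-out criterion.** With X binomial (32, p), this is P(X ≤ 6).

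Counting withdrawals only, whatever the silent loss:

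| Withdrawal rate | P(criterion met) |
|---|---|
| 5% | 0.999 |
| 10% | 0.964 |
| 15% | 0.805 |
| 20% | 0.535 |

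Counting everyone without OMAS:

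| Total missing | P(criterion met) |
|---|---|
| 20% | 0.535 |
| 30% | 0.113 |
| 35% | 0.036 |

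With 10% withdrawal and 20% silent loss (30% missing in all), the literal definition passes with probability 0.964 and the all-cause definition with 0.113.

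**4. Consequence for the sample sizes.** Evaluable per arm in the full trial = 60 × (1 − loss); power from the same t test.

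| Missing | Evaluable per arm | Power |
|---|---|---|
| 20% | 48 | 0.889 |
| 30% | 42 | 0.844 |
| 35% | 39 | 0.816 |

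The fair comparison is with 0.889 rather than 0.90, because 120 × 0.8 = 96, not 100: multiplying by 1.2 does not fully offset a 20% loss. That is a separate point. The excess loss costs 0.889 − 0.844 = 0.045 at 30% missing and 0.889 − 0.816 = 0.073 at 35%. The pilot would keep 32 × 0.70 = 22.4 evaluable at 30% missing, against the 26 it is sized for.

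**The case against.** **The adherence criterion may catch heavy loss.** Section 2.6.1 takes adherence over all participants in the allocated arm and assesses it by interview at the end of the study. If people who are not interviewed count as non-adherent, 85% of 32 is 27.2, so 28 must be shown adherent and at most 4 can be lost (both arms pooled for simplicity). P(X ≤ 4 of 32) at 30% loss is 0.019, even with perfect adherence among those interviewed. A reader might infer from the 0.96 that the pilot as a whole would almost surely be declared feasible; the documents do not support that. The 0.96 belongs to the drop-out criterion alone. Part of the concern survives, because the article does not say how people who are not interviewed are counted, and a participant can miss the three-month OMAS yet give the final interview.

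**The investigators would see the gap.** They will summarise OMAS on 32 participants and decide on continuation themselves (section 4), and follow-up is among the challenges the pilot is meant to identify (section 5). A reader might infer that the pilot would give no warning of missing data. That also goes too far. What stands is that the pre-stated criterion would still read as met.

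**The loss rates are assumed.** This is correct. Silent loss may be small: research visits fall at the same time points as clinic visits (Table 1), patients followed up elsewhere are excluded (section 2.3), and travel costs are reimbursed. Near-certain passing needs withdrawal of about 10% or less.

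**Withdrawal may be shorthand for any loss.** Possibly, in a condensed article whose flow chart is not shown. But the article states the formula for a primary outcome, and no text shown extends it to loss to follow-up.

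**Conclusion.** The point holds for the drop-out criterion. As written, its numerator omits participants lost without withdrawing, so it does not test the 20% planning figure in section 2.10. Under an assumed 10% withdrawal and 20% silent loss, it is met with probability 0.96, against 0.11 on an all-cause count. The first figure falls to 0.81 at 15% withdrawal and 0.54 at 20%. At 30% missing, the full trial would have about 84% power, compared with about 89% at the loss it planned for.

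The mismatch in definition rests on the text. The sizes rest on the assumed rates, independent participants, and the article's difference and SD. Nothing here shows that silent loss will be large or that all three criteria would pass together.

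**What to change.** In sections 2.6.1 and 3, define drop-out for the 20% criterion as the proportion of randomised participants without an evaluable OMAS at three months for any reason: withdrawal, loss to follow-up or a missed questionnaire. Report the six-month proportion alongside it, and formal withdrawals separately as a descriptive item.

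The cost is about a sentence in each section, and the data already come from the scheduled visits. The downside is that the criterion becomes somewhat harder to meet: at a true all-cause loss of exactly 20%, a pilot of 32 would meet it with probability of only about 0.54.
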